#### Secondary outcomes

2.10.2

The following will be assessed as secondary outcomes: changes in the VAS score for pain from baseline (visit 1) to visits 3 (third session) and 5 (fifth session); changes in the VAS score for pain at all assessment points from baseline (visit 1) to the follow-up visit (visit 7); changes in the ODI from visit 1 to visits 3, 5, and 7; and the change in ODI at all assessment points from visit 1 to visit 7.

### Safety

2.11

The occurrence of any adverse events will be evaluated at each visit. Patients will be monitored for undesirable, unintended signs, symptoms, and illnesses. The number and percentage of participants who experience at least 1 adverse event will be calculated.

### Withdrawal and dropout

2.12

Participants will be withdrawn from the trial if they do not meet the selection/exclusion criteria, withdraw consent, or conceive. The trial will be stopped if significant adverse events occur or if the patient is considered to be at risk upon further participation.

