#### Exclusion criteria

2.3.2

The exclusion criteria are as follows: a history of spinal surgery; progressive neurological deficit or severe psychiatric or psychological disorders; serious spinal disorders, such as metastatic cancer, vertebral fracture, spinal infection, and inflammatory spondylitis; other contraindications for treatment, such as clotting disorders, use of anticoagulants, and seizure disorders; presence of a device that could be affected by electromagnetic fields, such as a pacemaker or a hearing aid; use of medications that could affect the trial results, such as corticosteroids and anticonvulsants, within the last week; pregnancy, lactation, or plans for conception; participation in other clinical trials; and ineligibility judged by a physician.

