### Procedures

2.4

Patients with chronic low back pain will be recruited through advertisements on hospital bulletin boards and websites. Individuals interested in participating will be provided an explanation of the study until they have completely understood the risks and benefits. If they agree to participate, they will be asked to sign a consent form and undergo screening for eligibility. If they are found to be eligible, a study researcher will randomly allocate them to either the treatment or the sham group. The treatment procedure will be scheduled after randomization. The study flow chart is presented in Fig. 1.

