### Interventions

2.6

Both the EMA and sham groups will receive a total of 6 treatment sessions over 3 weeks, with 1 follow-up visit within 3 days after the last treatment (end of the clinical trial). The trial will be conducted under the same conditions for all participants, and the same practitioners will treat all participants. Other therapies and treatments associated with chronic low back pain will be excluded during the trial period. Use of medications other than those specified in the exclusion criteria (e.g., steroids, anticonvulsants) will be maintained. The acupuncture protocol to be used is based on the Standards for Reporting Interventions in Clinical Trials of Acupuncture (STRICTA) and is presented in Table 1.

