#### Primary outcomes

2.10.1

The change in the VAS score for pain from baseline (visit 1, first treatment session) to the follow-up visit after treatment completion (visit 7) will be assessed as the primary outcome.

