### Statistical analysis

2.14

Statistical analysis will be primarily based on the intent-to-treat principle, although per-protocol principles will also be checked. The missing values will be analyzed by the last observation carried forward method. The significance level will be set at *P* < .05, and the confidence interval at 95%. All statistical analyses will be performed using SPSS Statistics for Windows Version 20.0 (IBM Corp., Armonk, NY). There is no intermediate analysis of this study, and the final decision on end of trial is with principal investigator.

Differences in sociodemographic and baseline characteristics between the EMA and sham groups will be evaluated. For continuous data, Student *t* test or the Wilcoxon rank sum test will be performed. For categorical data, the Chi-square test or Fisher exact test will be used.

Changes in VAS and ODI scores from baseline to each assessment point will be assessed using Student *t* test or the Wilcoxon rank sum test, while those at all evaluation points from baseline to the follow-up visit will be assessed using repeated measures analysis of variance (RM-ANOVA). The incidence of adverse events will be investigated using the Chi-square test or Fisher exact test.

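### Section 2.12 ends trial participation, not only treatment, for ineligibility or conception, so these randomised patients reach the primary analysis only through carried-forward scores

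*Protocol article*

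**What the plan says.** Four parts of the protocol article bear on this.

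- **Withdrawal (2.12).** "Participants will be withdrawn from the trial if they do not meet the selection/exclusion criteria, withdraw consent, or conceive". The removal is from the trial. The section does not say whether any assessment follows, or what happens to the patient in the analysis.
- **Analysis (2.14).** "Statistical analysis will be primarily based on the intent-to-treat principle, although per-protocol principles will also be checked". On incomplete data: "The missing values will be analyzed by the last observation carried forward method".
- **Outcomes (2.10.1 and 2.10.2).** The primary outcome is the VAS change from visit 1 to visit 7. VAS and ODI changes are also assessed at visits 3 and 5.
- **Order and length (2.4 and 2.6).** Eligibility is checked before allocation: "If they are found to be eligible, a study researcher will randomly allocate them to either the treatment or the sham group". Both groups then receive "a total of 6 treatment sessions over 3 weeks, with 1 follow-up visit within 3 days after the last treatment".

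**The concern.** An intention-to-treat analysis needs outcomes from everyone randomised, as far as they can be collected. Of the three reasons in 2.12, only withdrawal of consent can stand in the way of a visit-7 assessment. A patient whose ineligibility comes to light late, or who conceives, can still mark a 100-mm line at a visit that is already scheduled. By ending participation for these two reasons, the rule discards primary-endpoint values that could have been observed, and 2.14 replaces them with an older score.

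Because the VAS assessments named after baseline are at visits 3, 5 and 7, a patient removed before visit 3 has only the baseline score to carry forward. The recorded change is then exactly zero, whatever the true course. The result is dilution of the treatment contrast and some loss of power. An analysis plan written later cannot recover values that the conduct rule stopped being collected.

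**Working it through.** **Inputs from section 2.13:** difference 0.87, SD 1.48, two-sided alpha 5%, power 80%, attrition 10%, 52 per group.

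**Assumptions, not in the document:**
- The two figures are on a 0-10 scale, so they equal 8.7 mm and 14.8 mm. The ratio, and hence power at constant SD, does not depend on this.
- The SD of the change equals 14.8 mm. This follows if the follow-up SD also holds at baseline and the correlation is 0.5.
- A share w of each arm is removed before visit 3. The document gives no rate.

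**Step 1. Reproduce the plan's figure.** n = 2(1.960 + 0.842)² × 1.48² / 0.87² = 45.4, so 46 per group. Then 46 / 0.9 = 51.1, so 52. The stated 52 per group is reproduced, and this point does not make it wrong.

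**Step 2. Power with all 52 per arm observed.** The standard error is 14.8 × √(2/52) = 2.90 mm. Power = Φ(8.7/2.90 − 1.96) = 85.0%. The t test gives 84.4%.

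**Step 3. Removed patients given zero change, SD held constant.** The expected difference becomes 8.7 × (1 − w). The last column drops the removed patients instead of carrying baseline forward.

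| w per arm | Expected difference | Power, zero change | Power, patients dropped |
|---|---|---|---|
| 0% | 8.70 mm | 85.0% | 85.0% |
| 2% | 8.53 mm | 83.6% | 84.3% |
| 5% | 8.27 mm | 81.3% | 83.2% |
| 10% | 7.83 mm | 77.0% | 81.2% |

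The 10% inflation covers the loss of patients from the analysis (81.2%). It does not fully cover their retention with a change of zero (77.0%).

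**Step 4. Let the SD change too.** Mixing zeros with real falls alters the spread. In an arm with mean fall m the variance is (1 − w) × 14.8² + w(1 − w) × m². For w = 10%, a sham fall of 20 mm and an active-arm fall of 28.7 mm:

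- sham: 197.1 + 0.09 × 400 = 233.1, SD 15.3 mm
- active: 197.1 + 0.09 × 823.7 = 271.3, SD 16.5 mm
- standard error: √((233.1 + 271.3)/52) = 3.11 mm
- power by the t test for a difference of 7.83 mm: about 70%

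Other assumed falls, by the t test:

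| Sham fall / active fall | w = 2% | w = 5% | w = 10% |
|---|---|---|---|
| 0 / 8.7 mm | 84% | 82% | 80% |
| 11.3 / 20 mm | 83% | 80% | 76% |
| 20 / 28.7 mm | 82% | 77% | 70% |
| 30 / 38.7 mm | 80% | 73% | 62% |

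One removal per arm is 1/52 = 1.9%, close to the w = 2% column. There the loss is between about 1 and 5 percentage points from 84.4%.

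**The case against.** **A reader might infer that 2.12 contradicts the intention-to-treat analysis.** The text does not support that. Section 2.12 says who leaves the trial, not who leaves the analysis set. With 2.14, a withdrawn patient stays in the randomised arm with a carried-forward value.

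**The rule may be meant partly for screening failures.** It speaks of participants, and consent comes before screening in 2.4. That randomised patients are covered is an inference from the section heading on withdrawal and dropout and from the order of steps in 2.4. It is the more natural reading, but not the only one.

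**Few patients should be affected.** Eligibility is checked before allocation, the exclusions already cover "pregnancy, lactation, or plans for conception", most other criteria are fixed history, and treatment lasts three weeks. This stands and limits the size of the point. The 10% in 2.13 is the allowance for attrition of every kind, so the 10% column is an upper illustration, not a forecast.

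**A reader might also infer bias between arms.** Three extra removals in one arm with an expected 20 mm fall would shift the contrast by 3/52 × 20 = 1.15 mm. Nothing in the document makes such an imbalance likely: section 2.5 blinds patients, treating staff and assessors. The exclusion left to a physician's judgement gives some room for removals that follow a patient's progress, but no arm-specific mechanism is shown.

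**The zero change comes from LOCF.** It does, and LOCF is a separate question. But the withdrawal rule is what makes these particular values missing.

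**A short article may leave end-of-study assessments to the full protocol.** That would answer a complaint about missing detail. Here the article states a rule, and as worded it ends participation.

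**Conclusion.** The point holds in a limited form. Section 2.12 ends participation for two reasons that do not prevent a visit-7 assessment. It thereby makes some primary-endpoint values missing by design and leaves the intention-to-treat analysis to rest on carried-forward scores for those patients. That weakens the analysis; it is not a contradiction.

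The size cannot be fixed from the document because no rate of such removals is given. At one or two patients per arm the loss of power is a few percentage points. The figures of 77% at constant SD, or 62% to 80% with the spread allowed to vary, need the whole attrition allowance to arise this way and before visit 3. A figure of about 70% further requires a 20 mm fall in the sham arm and 28.7 mm in the active arm; it should not be quoted as the expected consequence. The sample size of 52 per group is unaffected. This is a cheap improvement.

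**What to change.** Reword 2.12 to separate the end of study treatment from the end of participation:

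- Except where consent to further data collection is withdrawn, a randomised participant whose study treatment ends is still asked for the scheduled visit-7 VAS and ODI.
- That participant stays in the randomised arm for the intention-to-treat analysis.
- Participants found ineligible after randomisation are left out only of the per-protocol set.
- State that consented people who fail screening before allocation are screening failures, not withdrawals.

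When and why treatment is stopped is left as it is. The cost is a few sentences and one already scheduled assessment for a few patients. No new visit and no change in sample size is needed.

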### Sample size

2.13

The sample size will be calculated as per the results of previous trials on electroacupuncture therapy for chronic low back pain, because there are no available studies on electromagnetic acupuncture therapy. We assume that the effect of electromagnetic acupuncture would at least be equivalent to those of electroacupuncture; therefore, we will refer to the effect size of electroacupuncture therapy as conservative treatment for low back pain. In a previous study, the mean difference in the follow-up VAS score for pain was 0.87 between groups, with an estimated standard deviation of 1.48.^[17]^ The alpha level is 5% for both sides, and the study power is maintained at 80%. A total of 52 participants will thus be required in each group after considering an attrition rate of 10%.

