### Outcome measurements

2.10

The primary and secondary outcomes will be based on the VAS score for pain and the Oswestry Disability Index (ODI). The VAS has been shown to be a reliable tool for evaluating chronic pain.^[13]^ VAS for pain is a continuous scale with a horizontal or vertical line measuring 100 mm in length.^[14]^ Patients rate their current pain intensity from 0 (no pain) to 100 (worst pain imaginable).^[15]^ ODI was developed as a patient-oriented assessment tool and includes various questions that are answered by the patients themselves.^[16]^ The score is calculated as the total score/(number of questions provided by the author ∗ 5) ∗ 100.

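### The 80% power in section 2.13 rests on a difference in follow-up VAS, but the planned primary test is on unadjusted change from baseline, so the 80% is not shown for that test

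*Protocol article*

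**What the plan says.** Section 2.13 (Sample size) takes its inputs from an earlier electroacupuncture study: "the mean difference in the follow-up VAS score for pain was 0.87 between groups, with an estimated standard deviation of 1.48". It does not say whether that SD belongs to the follow-up score or to a change. The other settings are a two-sided 5% level ("The alpha level is 5% for both sides"), 80% power and 10% attrition, which lead to 52 per group.

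Section 2.10.1 (Primary outcomes) defines a different variable: "The change in the VAS score for pain from baseline (visit 1, first treatment session") to the follow-up visit, visit 7. Section 2.14 (Statistical analysis) compares changes from baseline to each assessment point by Student t test or Wilcoxon rank sum test. It names no baseline covariate. It also makes intention-to-treat the main analysis, with last observation carried forward for missing values.

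Section 2.13 gives the reason for borrowing the effect: no studies of electromagnetic acupuncture were available. It states the bridging assumption openly: "We assume that the effect of electromagnetic acupuncture would at least be equivalent to those of electroacupuncture".

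**The concern.** The sample size input is described as a difference between groups at follow-up. The planned test is on change from baseline. Randomisation makes the expected group difference the same for both, so 0.87 carries over. The SD does not. The SD of a change depends on how strongly baseline and follow-up correlate, and the article gives neither that correlation nor an SD of change.

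The stated power is a claim about the primary test. If the correlation is low, the trial has clearly less than 80% power, and a non-significant result would carry less weight than the stated figure suggests. If it is high, the trial has more power than it claims. Section 3 (Discussion) calls this a pilot meant to lay a foundation for a final trial, so a correct account of its precision would be useful there.

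**Working it through.** **Inputs from section 2.13:** difference 0.87; SD 1.48; two-sided alpha 0.05 (z = 1.960); power 80% (z = 0.842); attrition 10%. **Not in the article:** the baseline-to-follow-up correlation r, taken here as 0.3 to 0.7.

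**Step 1. Reproduce the plan's figure.**

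n per arm = 2 × (1.960 + 0.842)² × (1.48/0.87)² = 45.4, rounded up to 46.

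46 / 0.9 = 51.1, rounded up to 52. This matches section 2.13.

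The standardised effect is 0.87/1.48 = 0.588. Completers expected: 52 × 0.9 = 46.8, about 47 per arm. For a t test on a variable with SD 1.48, power with 47 per arm is 80.5%.

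**Step 2. SD of the variable actually tested.** Assume that 1.48 is the SD of the follow-up score and that baseline and follow-up variances are equal. Then

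SD of change = 1.48 × √(2(1 − r)).

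This equals 1.48 only at r = 0.5.

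**Step 3. SD under baseline adjustment.** For ANCOVA with baseline VAS as covariate,

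residual SD = 1.48 × √(1 − r²).

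This is never larger than 1.48 and does not need equal variances. The degree of freedom spent on the covariate is ignored; its effect is negligible at this size.

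**Step 4. Power for a true difference of 0.87 (two-sided 5%, t-based).**

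| r | SD of change | Change score, 47 per arm | Change score, 52 per arm | ANCOVA residual SD | ANCOVA, 47 per arm |
|---|---|---|---|---|---|
| 0.3 | 1.75 | 66% | 71% | 1.41 | 84% |
| 0.5 | 1.48 | 80% | 84% | 1.28 | 90% |
| 0.7 | 1.15 | 95% | 97% | 1.06 | 98% |

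The 52-per-arm column applies if carrying values forward keeps every randomised patient in the analysis and does not dilute the effect. In the limiting case r = 0, ANCOVA has residual SD 1.48 and power 80.5% with 47 per arm.

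**Step 5. The same dependence as a sample size.** For 80% power on the change score, including 10% attrition, the requirement is 72 per arm at r = 0.3, 52 at r = 0.5 and 32 at r = 0.7 (normal approximation, as in step 1).

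**The case against.** The strongest reply is that nothing has been miscalculated and that the gap may not exist. Section 2.13 does not say what 1.48 is the SD of. If the cited study reported an SD of change, the mismatch disappears. Even if it is a follow-up SD, power is 80% or more from r = 0.5 upwards. Equal variances are also an assumption. Section 2.3.1 admits only patients scoring at least 40 mm, which may narrow the baseline spread. With a baseline SD of 0.8 times the follow-up SD (assumed) and r = 0.3, the SD of change is 1.48 × √(1 + 0.64 − 0.48) = 1.59, and power with 47 per arm is about 74% rather than 66%. Finally, an article may leave the assumed correlation to the full protocol or analysis plan.

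Much of this stands. It rules out saying that the trial is underpowered or that the 80% is wrong. It does not remove the point: the article does state its input and its primary test, and as described they concern different variables with no link given. That is more than a detail left out.

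A reader might draw three stronger conclusions, and the article supports none of them.

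- **An error in the sample size arithmetic.** There is none; 52 reproduces.
- **An effect borrowed from the wrong comparison.** Under section 2.7 both arms are needled and only the stimulator differs, so one might infer that 0.87 overstates the increment over needling. But the comparator of the cited study is not stated. Section 1 says electroacupuncture has done better than conventional acupuncture, so 0.87 could itself be such an increment. The equivalence assumption is also disclosed.
- **A units error that affects power.** The figures look like a 0–10 scale, while section 2.10 uses 0 to 100. Rescaling changes the difference and the SD alike and leaves 0.588 untouched.

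**Conclusion.** The point holds as a gap in support: the 80% in section 2.13 is not shown for the unadjusted change-score test of sections 2.10.1 and 2.14. Its size depends on a correlation the article does not give. Over r = 0.3 to 0.7, power runs from 66% to 95% with 47 per arm, or from 71% to 97% if all 52 are analysed. These figures assume that 1.48 is the follow-up SD, that variances are equal at the two visits, and that the true difference is 0.87. They are for the t test; the Wilcoxon alternative was not computed. The direction of any error is unknown. The sample size of 52 per arm is correctly derived from its stated inputs and need not change.

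**What to change.** Keep N = 104. In section 2.14, make the primary analysis an ANCOVA of visit-7 VAS, or equivalently of its change, with baseline VAS as covariate. The two forms give the same treatment estimate, so the change outcome in section 2.10.1 can stay. In section 2.13, say that 1.48 is taken as the SD of the follow-up score and that the 80% applies to this analysis, where it is a lower bound at 47 per arm.

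If the unadjusted change-score test is kept, section 2.13 should instead give the SD of change, or the assumed r, and the power that follows from it. If 1.48 is already an SD of change, one sentence saying so settles the matter for that test; the claim that 1.48 is a follow-up SD should then not be made.

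The cost is more than wording: the first option changes the primary test in section 2.14 as well as the text of section 2.13. It needs no extra patients, visits or measurements, because baseline VAS is already required for the change score.

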### Statistical analysis

2.14

Statistical analysis will be primarily based on the intent-to-treat principle, although per-protocol principles will also be checked. The missing values will be analyzed by the last observation carried forward method. The significance level will be set at *P* < .05, and the confidence interval at 95%. All statistical analyses will be performed using SPSS Statistics for Windows Version 20.0 (IBM Corp., Armonk, NY). There is no intermediate analysis of this study, and the final decision on end of trial is with principal investigator.

Differences in sociodemographic and baseline characteristics between the EMA and sham groups will be evaluated. For continuous data, Student *t* test or the Wilcoxon rank sum test will be performed. For categorical data, the Chi-square test or Fisher exact test will be used.

Changes in VAS and ODI scores from baseline to each assessment point will be assessed using Student *t* test or the Wilcoxon rank sum test, while those at all evaluation points from baseline to the follow-up visit will be assessed using repeated measures analysis of variance (RM-ANOVA). The incidence of adverse events will be investigated using the Chi-square test or Fisher exact test.

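### Last observation carried forward, the only missing-data rule for the primary VAS analysis, biases the visit-7 difference: modestly if dropout is balanced, in either direction if it is not

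*Protocol article*

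**What the plan says.** Section 2.14 (Statistical analysis) sets the population first: "Statistical analysis will be primarily based on the intent-to-treat principle, although per-protocol principles will also be checked". The next sentence gives the whole missing-data rule: "The missing values will be analyzed by the last observation carried forward method". No assumption about why data are missing is stated, and no alternative handling is named.

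The rule feeds the primary outcome in section 2.10.1: "The change in the VAS score for pain from baseline (visit 1, first treatment session) to the follow-up visit after treatment completion (visit 7"). It also feeds the secondary outcomes in section 2.10.2, which include "changes in the VAS score for pain from baseline (visit 1) to visits 3 (third session) and 5 (fifth session") and the matching ODI changes. The scores available to carry forward to visit 7 are therefore those from visits 1, 3 and 5.

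The tests are also in section 2.14: "Changes in VAS and ODI scores from baseline to each assessment point will be assessed using Student *t* test or the Wilcoxon rank sum test". The profiles over all visits "will be assessed using repeated measures analysis of variance (RM-ANOVA").

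Section 2.13 allows for loss to follow-up: "A total of 52 participants will thus be required in each group after considering an attrition rate of 10" percent.

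**The concern.** Carrying a value forward assumes that a patient who leaves would have had no further change. The protocol expects the opposite. The Discussion speaks of pain reduction over time, and under section 2.7 both arms are needled at the same six acupoints, so the sham arm may improve as well. A patient lost after visit 1 is scored as zero change at visit 7 by construction. One lost after visit 3 or 5 is scored with only part of the change.

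At stake is the primary estimate. If both arms lose patients equally, part of a real effect is removed. If they do not, the arm with more dropout looks worse, whether or not the treatment works. Nobody can know the pattern in advance, so the rule cannot be defended as reliably conservative. The per-protocol check does not help, because it changes the population and leaves the missing-data assumption untested. The Discussion presents the trial as a foundation for a final trial, so a distorted effect could carry into that trial's design.

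**Working it through.** **The plan's own figure.** Section 2.13 gives a difference of 0.87, SD 1.48, two-sided 5% and 80% power. Then n = 2 × (1.96 + 0.8416)² × (1.48/0.87)² = 45.4, rounded up to 46 per arm. Allowing for attrition, 46/0.9 = 51.1, rounded up to 52. The stated 52 is reproduced.

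**Inputs.** From the protocol: 52 per arm, VAS at visits 1, 3, 5 and 7, and 10% attrition. The unit of 0.87 and 1.48 is not stated. I read them as 0–10 points, that is 8.7 mm and 14.8 mm on the 100-mm VAS. Assumed, because the protocol is silent:
- linear improvement, so that 0, 1/3 or 2/3 of the visit-7 change is present when the last score is at visit 1, 3 or 5;
- these three last visits equally likely, so a dropout keeps 1/3 of the change on average;
- correlation 0.5 between visits, so the SD of change is 14.8 × √(2 × 0.5) = 14.8 mm;
- dropout unrelated to pain within each arm;
- sham improvement S of 5, 10 or 20 mm.

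**Expected estimate.** With dropout d₁ on electromagnetic acupuncture (EMA) and d₀ on sham, the carried-forward difference is

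(S + 8.7) × (1 − d₁ + d₁/3) − S × (1 − d₀ + d₀/3).

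- 10%/10%: 8.7 × (0.9 + 0.1/3) = 8.12 mm for any S. If all dropouts leave after visit 1 it is 7.83 mm; if all leave after visit 5 it is 8.41 mm. The shrinkage is therefore about 3 to 10%.
- 15% EMA / 5% sham: 0.9 × (S + 8.7) − 0.9667 × S = 7.83 − S/15.
- 5% EMA / 15% sham: 0.9667 × (S + 8.7) − 0.9 × S = 8.41 + S/15. This exceeds 8.7 once S is above about 4.4 mm.
- No true effect, 15%/5% or 5%/15%: a spurious difference of S/15, against the arm with more dropout.

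**Power and type I error**, by simulation with a t test on change:

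| Sham improvement S | Estimate at 10/10 (mm) | Estimate at 15/5 (mm) | Power at 15/5 | Estimate at 5/15 (mm) | Spurious difference under the null, unequal dropout (mm) | Type I error at 15/5 |
|---|---|---|---|---|---|---|
| 5 mm | 8.12 | 7.50 | 72% | 8.74 | 0.33 | 4.9% |
| 10 mm | 8.12 | 7.16 | 68% | 9.08 | 0.67 | 5.4% |
| 20 mm | 8.12 | 6.50 | 54–55% | 9.74 | 1.33 | 7–8% |

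Estimates are from the algebra; simulated means agree to within about 0.1 mm. At 10%/10%, power is 75 to 79% across this range of S, and type I error stays at about 5%.

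**Comparator.** In the same simulated data, using only observed visit-7 scores gives about 8.7 mm, power of about 80% and type I error of about 5%, whether or not dropout is balanced. The loss in the carried-forward results therefore comes from the rule and not from the missing patients.

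**Standard error.** With no true effect and S = 20 mm, the empirical SD of the carried-forward difference is 2.99 mm and the mean estimated standard error is 2.97 mm, at both 10%/10% and 5%/15%.

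**The case against.** The strongest reply is about scale. Treatment lasts 3 weeks (section 2.6), planned attrition is 10% with no imbalance foreseen (section 2.13), and the Discussion calls the trial a pilot. With balanced dropout the rule shrinks a true effect modestly and produces no bias when there is none. The larger distortions need a threefold imbalance in dropout and grow with a sham response that the protocol does not state. At 8%/12% dropout the type I error is only 5.2 to 5.5%. All of this stands, and it limits the severity. It does not make the rule sound.

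A reader might infer more than the protocol supports:
- *That the standard errors are wrong because filled-in values are treated as observed.* It is true that no imputation uncertainty is carried. But each patient's carried-forward change is a single number whose spread the t test estimates properly, as the check above shows. The fault is mainly bias.
- *That false positives rise even when data are missing completely at random.* They do not at 10%/10%. Inflation needs dropout that differs by arm, and it is material only with a large sham response.
- *That the rule costs power measured from 85%.* That is the power of 52 per arm with nobody lost. The plan already budgets attrition, so the fair reference is about 80%.
- *That repeated measures ANOVA is a further failure because of sphericity.* It serves secondary outcomes and does not decide the primary test. Nothing here shows a violation, and any correction is ordinary analysis-plan detail.

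**Conclusion.** The point holds, as one that should be fixed. The rule is written into the protocol, so it is not a detail left to an unseen analysis plan, and it governs the primary estimate. At the planned 10% attrition in both arms, expect an estimate of about 8.1 mm in place of 8.7 mm and a loss of 1 to 5 points of power, with type I error intact. With unequal dropout the estimate can be too small (about 6.5 to 7.5 mm, power 54 to 72%, at 15% EMA / 5% sham) or too large (up to about 9.75 mm at 5% / 15%). With no true effect, those imbalances create a difference of 0.3 to 1.3 mm and a type I error of about 5 to 8%, the upper end only with a 20-mm sham response.

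These sizes depend on the assumed trajectory, correlation, sham response and dropout mechanism. Dropout related to pain itself was not modelled. That the direction of the bias cannot be known in advance does not depend on the exact values chosen.

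**What to change.** In section 2.14, replace the carried-forward rule for the primary analysis with a likelihood-based mixed model for repeated measures on all observed VAS values at visits 1, 3, 5 and 7. Enter visit 1 as a response, with the two group means constrained to be equal there, and take the group contrast in change to visit 7 as the primary estimate. A model that takes only patients with a post-baseline score would drop those lost after visit 1; treating visit 1 as a response keeps every randomised patient, in line with the intention-to-treat principle. Multiple imputation is an acceptable alternative. Handle ODI in the same way.

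Add one prespecified sensitivity analysis for data missing not at random, because the model still assumes that missingness is explained by the observed scores. Keep last observation carried forward as supplementary only. Repeated measures ANOVA may stay as a secondary description.

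The cost is revised wording and slightly more analysis work. No visit, measurement or patient is added. The change should be made before unblinding.
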